# Microwave Breast Imaging Using Rotational Bistatic Impulse Radar for the Detection of Breast Cancer: Protocol for a Prospective Diagnostic Study

**DOI:** 10.2196/17524

**Published:** 2020-10-19

**Keywords:** breast cancer, microwave imaging, diagnostic accuracy, screening, ultra-wideband radar

## Abstract

**Background:**

Mammography is the standard examination for breast cancer screening; however, it is associated with pain and exposure to ionizing radiation. Microwave breast imaging is a less invasive method for breast cancer surveillance. A bistatic impulse radar–based breast cancer detector has recently been developed.

**Objective:**

This study aims to present a protocol for evaluating the diagnostic accuracy of the novel microwave breast imaging device.

**Methods:**

This is a prospective diagnostic study. A total of 120 participants were recruited before treatment administration and divided into 2 cohorts: 100 patients diagnosed with breast cancer and 20 participants with benign breast tumors. The detector will be directly placed on each breast, while the participant is in supine position, without a coupling medium. Confocal images will be created based on the analyzed data, and the presence of breast tumors will be assessed. The primary endpoint will be the diagnostic accuracy, sensitivity, and specificity of the detector for breast cancer and benign tumors. The secondary endpoint will be the safety and detectability of each molecular subtype of breast cancer. For an exploratory endpoint, the influence of breast density and tumor size on tumor detection will be investigated.

**Results:**

Recruitment began in November 2018 and was completed by March 2020. We anticipate the preliminary results to be available by summer 2021.

**Conclusions:**

This study will provide insights on the diagnostic accuracy of microwave breast imaging using a rotational bistatic impulse radar. The collected data will improve the diagnostic algorithm of microwave imaging and lead to enhanced device performance.

**Trial Registration:**

Japan Registry of Clinical Trials jRCTs062180005; https://jrct.niph.go.jp/en-latest-detail/jRCTs062180005

**International Registered Report Identifier (IRRID):**

DERR1-10.2196/17524

## Introduction

### Background

The incidence of breast cancer is increasing, and the breast is the leading cancer location for women both worldwide and in Japan [1,2]. Mammography has been demonstrated to be effective in reducing breast cancer mortality and has become a standard screening method [3]. However, the screening rate of breast cancer varies greatly across countries; in Japan, it was 42.3% in 2016, which is lower than that in other developed countries [4,5]. The reasons for this lower rate of breast cancer screening could be the experience of pain by compression and exposure to ionizing radiation in mammography [6,7]. Therefore, painless and radiation exposure–free methodologies are required for the screening of breast cancer. In addition, mammography relies on the contrast in the X-ray attenuation coefficient between a normal mammary gland and malignant tissue, which can be as small as 1:1.1 [8]. This low contrast leads to lower sensitivity of mammography screening, particularly in dense breast tissue [6,7,9,10].

### Microwave Breast Imaging

Microwave breast imaging has developed significantly in the recent years [10,11]. The physical basis for microwave breast imaging consists of the difference in dielectric properties between the normal breast and cancerous tissues. The normal breast primarily consists of adipose tissue (low dielectric properties) with dispersed distributions of mammary glands (higher dielectric properties). Cancer tissue has greater dielectric properties at a frequency of 0.5GHz-50 GHz. A high contrast between healthy and cancerous tissues has been previously reported [12-17]. Among microwave breast imaging systems, the radar-based technology that uses time of flight of the impulse radio ultra-wideband (IR-UWB) signal is widely applied due to the simplicity and robustness of calculation [18-23]. This approach can calculate the amount of scattered electromagnetic energy at any spatial position to reconstruct an energy map of the object. The radar-based imaging method was developed in 1998, and it is referred to as confocal microwave imaging [18,19]. Synthetic focusing was performed under the assumption that the dielectric constant of breast was homogeneous. The electromagnetic signals scattered from the target location were calculated based on the signal path between the transmitter and receiver antennas and the average propagation speed of microwave radiation. This method reconstructs an energy map, which shows the qualitative position of the highest intensity of the confocal image of the scattered signals. In addition, the bistatic radar system, which allows different aspects of a target to be visualized, can deliver more information than the monostatic systems [24-29].

Some microwave breast imaging systems have already been evaluated in clinical settings. The largest cohort studies have been conducted with 86 and 223 patients using the Multistatic Array Processing for Radiowave Image Acquisition (MARIA) system [26,30]. Results indicated that the sensitivity of breast cancer detection was 74%-75%. Studies using other systems have also been conducted, and the results from 150 females with abnormal mammograms indicated a mean increase in the image contrast of 150%-200% between abnormal and normal breast tissues [31-33]. However, these conventional prototypes use vector network analyzers, resulting in heavy instrumentation and high cost. Although some groups have developed compact microwave imaging systems [27-29,34,35], these systems are yet to be applied in clinical settings.

### Preliminary Work

We developed a prototype handheld bistatic radar–based system using complementary metal–oxide–semiconductor (CMOS)-integrated circuits [36-41]. In a clinical pilot study, this system showed a 100% sensitivity in 5 patients with breast cancer [42]. Information on specificity and causes of false positives using this microwave imaging technology has not yet been clarified. Therefore, we aim to determine the diagnostic performance of our in-house bistatic radar–based detector with patients with breast cancer or those with benign breast tumors.

### Purpose

This study has 3 major goals. It aims to assess the sensitivity and specificity of the system in screening for breast cancer, assess the sensitivity and specificity of the system screening for benign tumors, and investigate the impact of tumor biology based on the measured results.

## Methods

### Study Design

This study is a single-center, single-arm, prospective diagnostic study on women with breast tumors and will be performed as a specified clinical trial under the Japanese law on clinical research (the Clinical Trials Act). Women with breast cancer or benign breast tumors as diagnosed by conventional examinations were recruited for this purpose. An examination using the handheld bistatic radar–based breast imaging system will be performed before any treatment. The flowchart and time schedule for this study are shown in Figure 1 and Table 1, respectively.

**Figure 1 figure1:**
[figure not shown]
Study flowchart.

**Table 1 table1:** Time schedule of the study.

Procedure	Baseline	Enrollment (week 0)	Intervention and assessment (week 0 to week 8)
Clinical breast imaging^a^	✓		
Pathological examination	✓		
Informed consent		✓	
Confirmation of eligibility criteria		✓	
Study examination			✓
Safety			✓

^a^Conducted by mammography, breast ultrasonography, contrast-enhanced breast magnetic resonance imaging, or fluorodeoxyglucose positron emission tomography.

The Certified Review Board of the Hiroshima University Hospital approved this study (CRB6180006) on October 3, 2018 (version 1). All procedures will be in accordance with the Japanese law (the Clinical Trials Act), the Declaration of Helsinki, and comparable ethical standards. This study is covered by clinical research insurance, and compensation is provided. Written informed consents will be obtained from all study participants.

### Study Population

Participants were recruited from the Hiroshima University Hospital and were classified into 2 groups: cohort 1, comprising 100 women with histologically diagnosed breast cancer; and cohort 2, comprising 20 women with histologically or radiologically diagnosed benign breast tumors.

The inclusion criteria included (1) female patients older than 20 years; (2) those with histologically confirmed breast cancer (only for cohort 1); (3) those with confirmed breast tumor by 1 or more arbitrary imaging examinations, such as mammography, breast ultrasonography, contrast-enhanced breast magnetic resonance imaging, or fluorodeoxyglucose positron emission tomography; and (4) those who provide a written informed consent. The exclusion criteria included (1) history of chemotherapy or radiotherapy within 6 months prior to registration; (2) hypersensitivity to the acrylonitrile butadiene styrene (ABS) plastic resin; (3) presence of a pacemaker; or (4) a physician’s decision. Participant examination will be discontinued and their data will be removed in case of withdrawal of consent, ineligibility, inability to participate in the study due to disease progression or complications, death, induction of treatment before the study, or any other exclusion criterion deemed necessary by the investigators. Benign breast tumors will be diagnosed by the Breast Imaging Reporting and Data System (BI-RADS) (ultrasound category 2 or less), fine-needle aspiration, or core needle biopsy. The radiological images will be read by 2 experienced radiologists.

### Study Examination

Measurements and weight of the handheld detector are 19.1 × 17.7 × 18.8 cm and 2 kg, respectively. It consists of a handle, step motor, control module, radio frequency module, and dome antenna array. The structure of the detector is depicted in Figure 2A. The system is composed of CMOS-integrated circuits that enable the generation and transmission of Gaussian monocycle pulse (GMP) trains and the control of the combination of a 4 × 4 cross-shaped dome antenna array, using a single-pole 8-throw switching matrix (SP8T-SW). The dome antenna array consists of 16 elements, and each antenna element is composed of a square slot set in a ground plane on 1 side of a Duroid RT 6010 substrate. The center frequency and the bandwidth of the ultra-wideband antenna are 6 GHz and 6.7 GHz, respectively. The dome shell is composed of ABS to hold the antennae in place. The dome antenna will be placed on each breast without any coupling liquid with the participant in a supine position and held by hand or supported by a stand to keep the device stationary. A transmitter antenna array emits GMP signals with the pulse duration of 160 picoseconds at a repetition frequency of 100 MHz to illuminate the breast tumor, and a receiver antenna receives the reflected signal. The antenna array rotates in 9 steps from 0° to 360° using a step motor. A single inspection can yield 40 sets of data with 2048 measurement points acquired within 5 minutes for each breast. The received signals are converted from analog to digital via a 12-bit analog-to-digital converter, and a confocal image is constructed (Figure 2B).

**Figure 2 figure2:**
[figure not shown]
Structure of the microwave breast tumor detector. ADC: analog-to-digital converter; CLK: clock; FPGA: field-programmable gate array; GMP: Gaussian monocycle pulse; LNA: low noise amplifier; PA: power amplifier; Ref. CLK: reference clock; RF: radio frequency; RX: receiver; SP8T: single-pole 8-throw; SW: switching; TX: transmitter.

### Study Endpoints

The primary endpoint is the detection sensitivity and specificity for breast cancer or benign breast tumors by the screening system. Contralateral healthy breasts will also be measured in this study, and the diagnostic accuracy will be calculated on a per-breast basis. The secondary endpoints are sensitivity for breast cancer detection according to the different molecular subtypes, sensitivity for benign breast tumors according to histology, and feasibility of the examination. The biology of breast cancer will be pathologically evaluated by surgery or using collected biopsy specimens. For exploratory purposes, the influence of tumor size and breast density on the detectability of breast tumor will also be investigated.

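### The data-removal rule makes no exception for the feasibility and safety endpoints, so it can bias feasibility upward and lose non-serious adverse events

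*Protocol article*

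**What the plan says.** Three parts of the protocol article bear on this point.

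- **Endpoints.** Study Endpoints lists, among the secondary endpoints, "feasibility of the examination". The Abstract words the secondary endpoint differently: it names safety and does not mention feasibility. Table 1 (Study Design) schedules safety in the week 0 to week 8 column.
- **Removal rule.** Study Population states: "Participant examination will be discontinued and their data will be removed in case of withdrawal of consent". The list goes on to ineligibility, then "inability to participate in the study due to disease progression or complications, death, induction of treatment before the study", and ends with "any other exclusion criterion deemed necessary by the investigators". The rule is not limited to any analysis set or endpoint.
- **Serious events.** Data Security and Analysis requires serious adverse events to be reported to the review board or the ministry. It says nothing about non-serious events, or about which women enter a safety analysis.

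The article gives no definition, numerator or denominator for feasibility.

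**The concern.** Leaving a woman out can be right for one endpoint and wrong for another. If she was never scanned, for a reason settled beforehand, she contributes nothing to sensitivity or specificity, and excluding her from the accuracy analysis can be legitimate. Feasibility asks a different question: of the women offered the examination, how many could have it done? A woman who withdraws partway through the scan, or who is stopped by a complication, is a feasibility failure and may also be a safety case. The removal rule takes out her data without asking which endpoint they serve.

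Two things are at stake. The feasibility figure can look better than what happened. Non-serious adverse events in removed women can also drop out of the safety account, because only serious events have a separate reporting route.

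**Working it through.** **The plan's own figures.** The article states no figure for feasibility, so there is none to reproduce. Its one computed figure is the 171 breasts in Sample Size Calculation. That reproduces as 0.80 × 0.20 × (1.96/0.06)² = 170.7, rounded up to 171, but it concerns sensitivity and has no bearing here.

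**Step 1: which removal reasons can contain a feasibility failure?**

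| Removal reason (Study Population) | Can it contain a feasibility failure? |
|---|---|
| Withdrawal of consent | Yes, if it happens during or because of the scan |
| Inability to take part (progression or complications) | Possibly, if a complication stops the scan; less so if illness prevents attendance |
| Investigator criterion | Yes, it is open-ended |
| Ineligibility, death, treatment started first | Says little about the device |

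Device failure, an incomplete scan, an unusable image and discomfort without withdrawal are not on the list. They stay in the data unless the investigator criterion is used.

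**Step 2: direction and size.** Let N be the women enrolled, f the feasibility failures and r the failures whose data are removed (0 ≤ r ≤ f). Then

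- feasibility with all women counted = (N − f)/N
- feasibility as reported = (N − f)/(N − r)

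The numerators are the same, and the second denominator is never larger than the first. Removing failures can therefore only raise the figure.

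N = 120 comes from the Abstract. The failure counts and the shares removed are assumptions, because the article gives neither.

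| f (assumed) | None removed | Half removed | All removed |
|---|---|---|---|
| 6 | 114/120 = 95.0% | 114/117 = 97.4% | 114/114 = 100% |
| 12 | 108/120 = 90.0% | 108/114 = 94.7% | 108/108 = 100% |
| 24 | 96/120 = 80.0% | 96/108 = 88.9% | 96/96 = 100% |

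**Step 3: does it matter against sampling error?** Exact 95% intervals for 12 failures:

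- none removed: 90.0% (83.2% to 94.7%)
- half removed: 94.7% (88.9% to 98.0%)
- all removed: 100% (lower bound 96.6%)

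With full removal, the 90.0% that counts everyone lies below the reported interval. With half removed it lies inside. With only 3 failures, all removed, 117/120 = 97.5% also lies inside the interval for 117/117, whose lower bound is 0.025^(1/117) = 96.9%. The distortion is clear only when failures are fairly numerous and most of them are removed.

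**The case against.** The strongest reply is that the removal rule is narrower than it first looks. The listed reasons lead to both discontinuation and removal, so a discontinued examination does not by itself cause data to be removed. For a scan of at most 5 minutes per breast (Study Examination), the obvious failures are technical, and these are not listed. The phrase "inability to participate in the study due to disease progression or complications" sits beside death and early treatment, and may simply mean that illness kept a woman from attending. Feasibility is also undefined in the article. It may be assessed descriptively, and the full protocol or analysis plan may set its denominator.

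Much of this stands, and it rules out several stronger readings that a reader might infer:

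- **Feasibility must come out at 100%, or cannot show a problem.** This requires every failure to meet a removal reason. The text does not say so.
- **Feasibility is computed on completers only.** The article does not say this, and the lack of a definition is not a fault in a condensed article.
- **All complications disappear.** Serious adverse events are still reported under Data Security and Analysis.
- **Limiting removal to reasons arising before the scan would not help feasibility.** It would help, because failures during scanning would then be kept.

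The reply does not remove the conflict between two explicit statements. The rule is unqualified, it covers withdrawal during the scan, and it ends in an investigator criterion that can reach any failed examination. A definition held elsewhere would help only if it overrode the rule as written.

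**Conclusion.** The concern holds as a possible upward bias of uncertain size. As written, the rule can remove feasibility failures and non-serious adverse events, and it cannot bias feasibility downward by removing failures. With an assumed 12 failures in 120 women, the overstatement runs from nothing, through 4.7 percentage points if half are removed (94.7% against 90.0%), to 10 points if all are.

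This rests on three assumptions: feasibility is reported as a proportion of women, the failure counts are illustrative, and the rule is applied literally to every endpoint. Nothing in the article shows how many failures occurred or how often the investigator criterion was used. As this affects secondary endpoints and is cheap to repair, it should be corrected, but it does not threaten the primary accuracy result.

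**What to change.** Add to Study Population and Study Endpoints that:

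1. Data removal applies to the accuracy analysis set only.
2. The denominators for feasibility and safety are all consented, eligible women.
3. An examination started but discontinued, or yielding no usable image, counts as a feasibility failure, with its reason.
4. Examinations never started are reported separately by reason (for example death, treatment started first, progression). Scoring all of them as device failures would bias feasibility downward.
5. Adverse events already observed are kept.
6. A woman who withdraws permission to use her data is reported only as a count.

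The cost is a wording change and one small table of examination status and reason per enrolled woman, with no new procedures. Recruitment ended by March 2020, but the table can still be made, provided that enrollment records hold status and reason. The feasibility figure may become less favorable.

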### Sample Size Calculation

Sample size calculations were based on the sensitivity of breast cancer detection and the significance of breast cancer screening. The expected sensitivity was set at 80% with reference to the sensitivity of the Japanese mammography screening [43]. The required sample size was 171 breasts according to a width of the 95% CI being set to 0.12 at one-sided α=.05. Therefore, a sample size of 100 women (200 breasts) in cohort 1 was proposed.

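### The 171 breasts required for sensitivity are met by counting healthy breasts; about 100 cancer-bearing breasts give a 95% CI width of about 0.16, not 0.12

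*Protocol article*

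**What the plan says.** All references are to the protocol article.

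- **Basis of the calculation (Sample Size Calculation).** "Sample size calculations were based on the sensitivity of breast cancer detection and the significance of breast cancer screening". The input is 80%: "The expected sensitivity was set at 80% with reference to the sensitivity of the Japanese mammography screening".
- **Requirement (same section).** "The required sample size was 171 breasts according to a width of the 95% CI being set to 0.12". The same sentence attaches a one-sided α of .05 to this interval.
- **Conversion to women (same section).** "Therefore, a sample size of 100 women (200 breasts) in cohort 1 was proposed".
- **Unit of analysis (Study Endpoints).** "Contralateral healthy breasts will also be measured in this study, and the diagnostic accuracy will be calculated on a per-breast basis".
- **Who is enrolled (Study Population).** Cohort 1 is 100 women with histologically diagnosed breast cancer, with no requirement that both breasts be affected. Cohort 2 is 20 women with benign tumors.
- **Blinding (Limitations).** Analysts will not know whether the tumor is on the left or the right, which fits one affected side per woman.

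**The concern.** Sensitivity is the proportion of diseased units that test positive. In a per-breast analysis of cancer detection, its denominator is the number of breasts with cancer. A healthy contralateral breast contributes to specificity and tells us nothing about sensitivity. The plan derives a requirement for sensitivity and then meets it with both breasts of each woman, roughly half of which are healthy by its own description.

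This is the only precision statement in the document, and it concerns a primary endpoint. If it is wrong, the design lacks the precision it claims. A report that carried 171 or 200 breasts forward as the basis for sensitivity would overstate how well the main result is known.

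**Working it through.** **Inputs**

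| Quantity | Value | Source |
|---|---|---|
| Expected sensitivity, p | 0.80 | Sample Size Calculation |
| Full 95% CI width | 0.12 (half-width h = 0.06) | Sample Size Calculation |
| Required breasts | 171 | Sample Size Calculation |
| Cohort 1 | 100 women, counted as 200 breasts | Sample Size Calculation; Study Population |
| Second breast | healthy contralateral | Study Endpoints |
| Bilateral cancer rate | not given; 0% to 10% assumed | assumption |

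**Step 1. Reproduce 171.** For a normal-approximation (Wald) interval, n = z² p(1 − p) / h².

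1.96² × 0.80 × 0.20 / 0.06² = 170.7, rounded up to **171**. The plan's figure is reproduced exactly.

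**Step 2. Test other readings of the sentence.**

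| Reading | n required |
|---|---|
| z = 1.96, half-width 0.06 | 171 |
| z = 1.645 (one-sided .05), half-width 0.06 | 121 |
| z = 1.96, half-width 0.12 | 43 |
| z = 1.645, half-width 0.12 | 31 |

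Among these, only a two-sided 95% interval of full width 0.12 gives 171.

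**Step 3. Count the breasts that inform sensitivity.** One affected breast per woman gives 100. Bilateral cases add to this: 102, 105 or 110 breasts if 2%, 5% or 10% of women have bilateral cancer. Cohort 2 adds none. Reaching 171 from 100 women needs 171 − 100 = 71 bilateral cases.

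**Step 4. Width actually delivered at 80%.** Wald width = 2 × 1.96 × √(0.16 / n).

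| Cancer-bearing breasts | Wald | Wilson | Exact (Clopper-Pearson) |
|---|---|---|---|
| 100 | 0.157 | 0.156 (0.711 to 0.867) | 0.165 (0.708 to 0.873) |
| 110 (10% bilateral, assumed) | 0.150 | 0.148 | 0.157 |
| 171 | 0.120 | 0.119 | 0.125 |
| 200 | 0.111 | 0.110 | 0.115 |

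The ratio for 100 breasts is 0.1568 / 0.12 = 1.31, so the interval is about 31% wider than planned. The 200-breast row would apply only if every breast carried cancer.

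**Step 5. A lower sensitivity.** The Introduction reports 74%-75% for an earlier microwave system. At 75%, 100 breasts give 2 × 1.96 × √(0.1875 / 100) = 0.170. A width of 0.12 would then need 1.96² × 0.1875 / 0.06² = 200.08, that is 201 cancer-bearing breasts.

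**Step 6. Women needed for 0.12 at 80%.** 171 women if all disease is unilateral; 168, 163 or 156 if 2%, 5% or 10% have bilateral cancer (171 divided by 1.02, 1.05 or 1.10, rounded up).

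**The case against.** **The sentence contradicts itself on sidedness.** It pairs a 95% CI with a one-sided α of .05. With z = 1.645 the shortfall is smaller: 100 breasts give a width of 0.132, about 10% over target. But that reading needs 121 breasts and does not produce 171, and the target is still missed. The conflict is a separate defect in the same sentence, and the corrected text should resolve it openly.

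**The 200 breasts could serve overall accuracy.** The abstract lists diagnostic accuracy among the primary endpoints, and all cohort 1 breasts count toward that. However, the section names sensitivity as its basis and uses an expected sensitivity as its input.

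**The consequence is limited.** No test, power claim or decision rule depends on the 0.12 width. No analysis rule puts healthy breasts into the sensitivity denominator, and a correctly computed interval in the report will show the true uncertainty. Recruitment is over, so the sample size cannot change. This all stands, and it means the error lies in the design justification rather than in a stated analysis. It does not make the justification true.

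**Some supporting figures rest on assumptions.** The bilateral rate and any expected specificity are not in the document. This is also correct, and they are labelled as assumptions here. The shortfall in sensitivity does not depend on either: it holds across the whole 0% to 10% bilateral range.

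**Conclusion.** The concern holds. The number 171 is right for cancer-bearing breasts, and the conversion to 100 women is wrong because it counts healthy breasts. At 80% sensitivity the design delivers a 95% CI width of about 0.16 (0.157 Wald, 0.156 Wilson, 0.165 exact) against the stated 0.12. The half-width is 0.078 rather than 0.06.

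This assumes about one cancer-bearing breast per woman, as the description of the contralateral breasts implies. With up to 10% bilateral disease the Wald width is still 0.150. No reading of the sentence that reproduces 171 lets 100 women with mainly unilateral cancer meet the target. Because this is the only precision figure given, and it is for a primary endpoint, it should be corrected.

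**What to change.** Revise the Sample Size Calculation section as follows.

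1. Replace the conversion to women with: *Cohort 1 provides about 100 cancer-bearing breasts; at an expected sensitivity of 80% the two-sided 95% CI has a full width of about 0.16 (about 0.17 at 75%).*
2. Delete the implication that 200 breasts satisfy the 171-breast requirement.
3. Remove the one-sided α, since 171 comes from a two-sided 95% interval.
4. State that the denominator for cancer sensitivity is cancer-bearing breasts only.
5. Give the precision for specificity separately and name its denominator. Healthy contralateral breasts number about 100 + 20 = 120 across both cohorts, less any bilateral cases. The document gives no expected specificity, so any value is an assumption: with 120 breasts the Wald width is 0.107 at 90%, 0.143 at 80% and 0.179 at 50%. If breasts with benign tumors also count as cancer-negative, the denominator is about 140 and the width at 80% is 2 × 1.96 × √(0.16 / 140) = 0.133.

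The cost is wording only. The stated precision becomes less favorable, 0.16 instead of 0.12, and no further patients are needed.
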